### Study Design and Participants

To evaluate the Screen-Free Time With Friends intervention, we conduct a cluster RCT involving children aged 9‐11 years from public schools across Denmark. The initial recruitment target was 18 schools, based on sample size calculations using our primary outcome: time spent with peers (in minutes). Schools are randomized by an independent statistician in a 1:1 ratio to either an intervention or a control group, balancing on the following criteria: (1) number of students in 3rd grade, (2) school-level parents’ ethnicity, (3) school-level parents’ education level, and (4) building coverage. A covariate-constrained randomization procedure is applied [19] to optimize the balance in school-level covariates between the intervention and control groups, thereby reducing the likelihood of substantial differences in child baseline characteristics. Data on school-level covariates are sourced from the Danish Ministry of Children and Education [20]. The statistician communicates the allocation results to the research team in two rounds, after the respective schools have completed their baseline assessments. Following randomization, after-school clubs and local community stakeholders affiliated with the schools in the intervention group are recruited to participate in the intervention. The respective school, after-school club, and local community will hereafter be referred to as an intervention school district. Intervention school districts implement the intervention program, consisting of five core components—(1) curricular activities, (2) two family meetings, (3) a brief exercise for parents, (4) an after-school club developmental program, and (5) two workshops in the local community—while school districts randomized to the control group continue with their usual practices.

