### Statistical Methods and Analysis

#### Sample Size Calculation

We anticipated a total of 1080 eligible 3rd-grade children, assuming an average of 2.5 classes per school and 24 students per class in each of the 18 schools. With an expected participation rate of approximately 80%, we aimed to enroll 864 children at baseline. Accounting for an estimated 15% dropout or missing data rate, we projected an average of 41 children per school (cluster) in the final analytical sample, resulting in a total sample size of approximately 738 children. Drawing on a previous Danish school-based study conducted by our research group [45], we assumed a coefficient of variation in cluster size of 0.24 and an intracluster correlation coefficient of 0.07. The intraclass correlation coefficient estimate was based on internal calculations from that study using a related behavioral outcome (physical activity), as direct estimates for the present primary outcome were not available. Additionally, based on findings from the feasibility trial, we estimated a correlation of 0.67 between baseline and follow-up measurements, and a standard deviation of 38 minutes per day in both the intervention and control groups. To control for type I error due to the small number of clusters, we lowered the α level to .025 in the power calculation. This adjustment was made in anticipation of applying the Satterthwaite correction for mixed linear models, as recommended for small-sample cluster trials [46]. Under these assumptions, the study is powered at 80% to detect a statistically significant mean difference of 13.5 minutes per day or more between the intervention and control groups at follow-up. A difference of 13.5 minutes per day corresponds to approximately 1.6 additional hours of peer interaction per week, roughly equivalent to one extra weekly after-school playdate or an extra organized extracurricular activity. Such changes may be meaningful, as previous research has shown that engaging in social leisure activities, including meeting friends at least once a week, is positively associated with adolescents’ well-being and perceived peer support [47]. Moreover, social connection has been consistently associated with better physical and mental health [48]. This interpretation is further supported by Danish data indicating that a substantial proportion of 11-year-olds have relatively low levels of face-to-face interaction with peers, with approximately 50% reporting that they meet friends once a week or less, or not at all [9]. Together, this supports that the chosen effect size may represent a meaningful change in children’s everyday social interaction.

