##### Primary Analysis

Mixed effects regression models will be used to estimate between-group differences from baseline to follow-up in time spent face-to-face with peers. Models will be adjusted for weekday and include school, participant ID, and measurement round as random effects to account for clustering and repeated measurements. Imbalanced covariates will be included as fixed effects if relevant. The Satterthwaite correction will be applied to account for the small number of clusters, as recommended [46]. All analyses will follow the intention-to-treat principle.

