##### Secondary Analyses

Analyses of secondary outcomes will follow the same modeling approach as the primary analysis. Adjustment for multiple testing will be applied using the Holm step-down procedure to control the familywise error rate at a 2-sided significance level of α=.05. Adjusted *P* values will be reported for the secondary end points, and findings will be reported alongside the primary outcome to aid interpretation of the results.

For the additional outcomes (eg, physical activity and well-being), models will include school and participant ID as random effects. No adjustment for multiple testing will be applied for these outcomes, and findings will be interpreted as exploratory.

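### As listed, the primary model's random effects do not let schools differ in their change over time, so the arm-by-time test is run at child level and Satterthwaite cannot reflect the 18 schools

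*Protocol article*

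**What the plan says.** All places are in the Protocol article.

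- **Unit of randomisation** (Study Design and Participants): "Schools are randomized by an independent statistician in a 1:1 ratio". With 18 schools this gives 9 per arm.
- **Target of the primary model** (Primary Analysis): to "estimate between-group differences from baseline to follow-up in time spent face-to-face with peers". The Primary Outcome and Secondary Outcomes sections fix the end point as baseline to 13-15 months.
- **Random effects** (Primary Analysis): models will "include school, participant ID, and measurement round as random effects to account for clustering and repeated measurements".
- **Small-sample correction** (Primary Analysis): "The Satterthwaite correction will be applied to account for the small number of clusters".
- **Secondary outcomes** (Secondary Analyses): the four confirmatory secondary outcomes use the same modelling approach. For the additional, exploratory outcomes, "models will include school and participant ID as random effects".
- **Power** (Sample Size Calculation): "we projected an average of 41 children per school (cluster) in the final analytical sample", with "an intracluster correlation coefficient of 0.07". Alpha is lowered to .025 in anticipation of the Satterthwaite correction.

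**The concern.** In a cluster trial analysed as change over time, the uncertainty that matters at school level is how much schools differ in their *change*. A school intercept describes only how much they differ in *level*. If the model has no term for school-specific change, any local shift between the two rounds is counted as independent information from each child.

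Such shifts are plausible here. After-school club time is one of the three summands of the primary outcome. The Discussion says that most public schools move children to another type of club between grades 3 and 4, when participation falls most, and the trial spans that transition. Baseline ran from December to June and follow-up from March to August, so the seasonal shift may also differ between schools.

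At stake are the standard error, the degrees of freedom and the true type I error of the primary test and of the four confirmatory secondary tests. The design also allows for school clustering in the detectable difference, so the test should carry the same allowance.

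**Working it through.** **Inputs.** From Sample Size Calculation: SD 38 min/day (variance 1444), correlation r = 0.67, ICC 0.07, 41 children per school, 369 per arm. From Results: 343 children with an enrolled parent at baseline, so 343/18 ≈ 19 per school. *Assumed, because the article does not give it:* the school autocorrelation c, which is the correlation of a school's effect at baseline with its effect at follow-up.

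**1. The plan's own figure.** Baseline-adjusted SD = 38 × √(1 − 0.67²) = 28.2. Design effect = 1 + 40 × 0.07 = 3.80. SE = 28.2 × √(2 × 3.80/369) = 4.05. With two-sided alpha .025, 80% power and 16 df (noncentral t), the detectable difference is 13.57 min, against 13.5 stated. Allowing for a cluster-size coefficient of variation of 0.24 gives 13.86. Change scores at alpha .05 with that allowance give 13.51. All three routes include a school design effect and 16 df.

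**2. What the listed terms do to the contrast.** Write the outcome of child i in school s at round t as fixed part + u(s) + v(i) + w + error, where w is the round effect. In follow-up minus baseline, u(s) and v(i) cancel. If w is nested in the child, it is child-level noise. If it is one effect shared by all children, it is the same in both arms and cancels between them. In neither case does a school-level term remain.

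**3. Standard error and df as listed.** Variance of change = 2 × 1444 × (1 − 0.67) = 953. SE = √(953 × 4/343) = 3.33 min. A generalised least squares calculation on 343 children with unequal school sizes gives 3.34 whether the school share of variance is set to 0, 0.07 or 0.30. Satterthwaite df are 343 − 2 = 341 with complete data, and 299 to 269 if 15-30% of children are seen in only one round. With a school-by-round term and c = 0.8, the SE is 4.51 and the df 15.8.

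**4. Type I error.** ICC of the change = 0.07 × (1 − c)/0.33. Design effect = 1 + 18 × that ICC. True error ≈ 2 × [1 − Φ(1.96/√design effect)].

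| c | ICC of change | Design effect | SE understated by factor | Type I error |
|---|---|---|---|---|
| 1.0 | 0 | 1.00 | 1.00 | 5% |
| 0.95 | 0.011 | 1.19 | 1.09 | 7-8% |
| 0.90 | 0.021 | 1.38 | 1.18 | 9-10% |
| 0.80 | 0.042 | 1.76 | 1.33 | 14% |
| 0.67 | 0.070 | 2.26 | 1.50 | 19-20% |
| 0.50 | 0.106 | 2.91 | 1.71 | 25-26% |

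Where a range is shown, it covers the closed form and separate simulations. At the planned 41 per school, with varying school size, the error is larger: about 16% at 0.90, 24% at 0.80 and 32% at 0.67. A t-test on school mean changes stays between 4% and 6% throughout.

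**5. Degrees of freedom to expect with the term added.** The school-by-round stratum has (18 − 2) × (rounds − 1) df: 16 if only baseline and 13-15 months are modelled, and 32 with all three rounds and a common school-by-round variance.

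**The case against.** The strongest reply is that a condensed article names three grouping factors without giving their nesting or a fixed-effects formula, and two models consistent with that silence would escape the problem.

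- **Round fitted within school, or a school-level slope.** That is a school-by-round effect, and the point would fall. The text does not say it. Secondary Analyses drops round for the additional outcomes, which suggests that round is there to handle repeated days within a child. A school-by-round effect would still have been estimable for those outcomes.
- **Baseline as a covariate.** The school intercept would then stay in the contrast. The power statement concerns a difference at follow-up and is reproduced by a baseline-adjusted formula, so this reading is possible. But baseline is not listed as a covariate, and the hypotheses, the end point and the model sentence all speak of change from baseline.

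Constraining the arms to equal baseline means lets the school intercept in only slightly. The SE goes from 3.03 to 3.22 min as the school share goes from 0 to 0.07, and the df stay near 353.

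Three stronger inferences are tempting, and the article does not support them:

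- *Type I error is certainly well above 5%.* Inflation needs c below 1, and c is not given. At c = 1 there is none.
- *The plan's own ICC implies 19%.* That requires 0.07 to be the ICC of change. The stated 13.5 min can be reproduced without that assumption, and the 0.07 was borrowed from physical activity.
- *The 13-15 month contrast is left unclear.* The Primary Outcome and Secondary Outcomes sections fix it.

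**Conclusion.** The point holds in conditional form. With the random effects as listed and a change-from-baseline contrast, the primary test is effectively at child level (about 270-341 df), and the Satterthwaite correction cannot do what the article says it is for. If schools drift differently over time, the standard error is too small. Under ICC 0.07, r = 0.67 and 19 children per school, true type I error runs from 5% (c = 1) through about 14% (c = 0.80) to about 25% (c = 0.50). Where in that range the trial lies cannot be settled from the article. The four confirmatory secondary outcomes inherit the problem. The exploratory models also lack the term, but they carry no confirmatory claim and matter less. The conclusion rests on round being nested in the child or shared by all children, and on baseline being an outcome row instead of a covariate. Both are the more natural readings, but neither is spelled out.

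**What to change.** Replace the model sentence in Primary Analysis with a full specification:

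- **Fixed effects:** round (categorical), arm-by-round, weekday.
- **Random effects:** school, school-by-round, participant, participant-by-round.
- **Estimation:** REML with Satterthwaite df.
- **Primary test:** the arm contrast in change from baseline to 13-15 months, as the end point already states.

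Use the same model for the four confirmatory secondary outcomes. As a lower priority, add school-by-round to the exploratory models.

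As a check, confirm that the reported df are at school level: about 16 with two rounds modelled, or about 32 with all three and a common school-by-round variance, and not in the hundreds. Report a t-test on school mean changes as a sensitivity analysis. It should be similar but need not match exactly, particularly when three rounds share one variance.

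**Cost:** one sentence, and no new data. The article states that as of March 2026 analysis has not begun, so the change can still be made in advance. Confidence intervals will be wider: in the example above the SE rises from 3.34 to 4.51 min at c = 0.8. If the authors already intend this model, writing it down costs nothing.

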##### Secondary Analyses

Analyses of secondary outcomes will follow the same modeling approach as the primary analysis. Adjustment for multiple testing will be applied using the Holm step-down procedure to control the familywise error rate at a 2-sided significance level of α=.05. Adjusted *P* values will be reported for the secondary end points, and findings will be reported alongside the primary outcome to aid interpretation of the results.

For the additional outcomes (eg, physical activity and well-being), models will include school and participant ID as random effects. No adjustment for multiple testing will be applied for these outcomes, and findings will be interpreted as exploratory.

##### Missing Data

For the primary and secondary outcomes, participants with at least one valid day of SMS-based data will be included in the analysis. Mixed effects models allow inclusion of participants with varying numbers of observed days, thereby retaining available information and maximizing statistical power.

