**Results:**

The project was funded in July 2020. Schools were recruited from July 2023 to January 2024, while children and parents were recruited from November 2023 to April 2024. At baseline, 685 children were enrolled at the participating schools, with 343 (50%) having at least one parent enrolled in the questionnaire. The primary outcome is therefore assessed among a subset of participants, which may affect the effective sample size. Baseline data were collected from December 2023 to June 2024, and follow-up data from March to August 2025. As of March 2026, data analysis has not yet commenced, and no study results are currently available. Findings are expected to be published by the end of 2026.

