
#### Baseline Characteristics

Baseline characteristics will be presented descriptively for the intervention and control groups using appropriate summary statistics. In addition, the balance for the school-level covariates included in the constrained randomization procedure (number of students in 3rd grade, parental ethnicity, parental education level, and building coverage) will be reported.

To assess sample representativeness, baseline characteristics will be compared between children with at least one participating parent and those without participating parents using data available for the majority of children. These comparisons will include selected child-reported measures (eg, indicators of well-being and leisure activities), as well as teacher-reported Strengths and Difficulties Questionnaire scores.

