## Results

This cluster RCT was funded in July 2020 as part of a larger project that also included a formative qualitative study, an intervention development process, and a feasibility study [17,18]. For this cluster RCT, schools were recruited from July 2023 to January 2024, and children and parents were recruited from November 2023 to April 2024. At baseline, 685 children were enrolled at the participating schools (Table 3). During the study period, 50 transferred to nonparticipating schools, while 32 were newly enrolled at participating schools, resulting in 667 children being enrolled at the participating schools at follow-up. In addition, 2 children moved between schools within the study. All children participated in most of the measurements unless they were actively withdrawn by their parents or absent from school on the day the measurements were conducted. Table 3 provides further details about the participant groups, including the number of children with consent to participate in the physical activity measurements, as well as the number of children with at least one parent who voluntarily enrolled to complete questionnaires and install the Avicenna app.

Baseline data were collected from December 2023 to June 2024. Schools were randomized in March 2024, with allocation results communicated to the research team in two rounds (round 1: 7 schools; round 2: 11 schools). The scheduling and implementation of the intervention activities ran from March to May 2024, when the children were in 3rd grade (ages 9‐10 years), to March 2025, when they completed 4th grade (ages 10‐11 years). The exact timing of intervention activities varied by school district, as scheduling was coordinated with schools, after-school clubs, and local communities to ensure feasibility. Follow-up data collection took place from March 2025 to August 2025. A study timeline is presented in Figure 2 [49]. Interim data checks have been performed to ensure data quality; however, no formal statistical analyses of intervention effects have been conducted (as of March 2026).

**Table 3. T3:** Participation status of children and parents at baseline and follow-up.

Participating children	Baseline, n (%)	Follow-up, n (%)
Children enrolled at the participating schools	685 (100)	667 (100)
Children *not* withdrawn by parents	675 (99)	642 (96)
Children with consent to participate in accelerometer measurements	366 (53)	372 (56)
Children with ≥1 parent enrolled in questionnaire	343 (50)	351 (53)

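### The one-valid-day inclusion rule has no baseline or registration-date condition, so it admits children whose parents first registered after allocation was released; a cheap restriction of the primary set removes the risk

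*Protocol article*

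**What the plan says.** Under Missing Data, the protocol article includes a child in the primary and secondary analyses on one condition: "participants with at least one valid day of SMS-based data will be included in the analysis". It does not say at which time point that day must fall or when the parent must have registered. Primary Analysis adds "All analyses will follow the intention-to-treat principle" without saying which children form the set. Primary Outcome defines the end point as the between-group difference from baseline to 13-15 months.

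SMS data come only from parents who register voluntarily (Ethical Considerations). Results dates recruitment: "children and parents were recruited from November 2023 to April 2024". Schools were randomised in March 2024, and allocation was released to the research team in two rounds, after the schools concerned had completed baseline (Study Design and Participants; Results).

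Results also reports movement between schools, "50 transferred to nonparticipating schools, while 32 were newly enrolled at participating schools", "resulting in 667 children being enrolled at the participating schools at follow-up". The Table 3 row "Children with ≥1 parent enrolled in questionnaire" reads 343 (50%) at baseline and 351 (53%) at follow-up.

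For representativeness, "baseline characteristics will be compared between children with at least one participating parent and those without participating parents". The only analysis listed to test the primary result is an ordinal model (Sensitivity Analyses).

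**The concern.** The end point is a change from baseline, but the rule lets in children who have no baseline and who entered after randomisation. The registered count rose while children were leaving, so such entrants exist on paper. Because allocation is released after each school's baseline, registrations added after the baseline count fall largely or wholly after release.

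Control districts continue as usual. Intervention parents alone are invited to two family meetings (Intervention Component 2) and take part in an exercise intended to raise awareness of the project (Intervention Component 3). The number and kind of late-registering families could therefore differ between arms. The same parents report the primary outcome and all four confirmatory secondary outcomes. Children who joined the schools later would also have had only part of the intervention.

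At stake is whether the children compared at follow-up are still those whose schools were randomised, with data obtained independently of the allocation.

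**Working it through.** **1. Reproduce the flow (Results, Table 3).** 685 − 50 + 32 = 667, which agrees with the article.

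**2. New registrations.** Let L be the registered children among the 50 leavers and A the children first registered after the baseline count. If no other registrations were lost, 351 = 343 − L + A, so A = 8 + L, with L between 0 and 50.

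| Assumption on leavers | L | A | A as share of 351 |
|---|---|---|---|
| None registered | 0 | 8 | 2.3% |
| Registered at the baseline rate: 50 × 343/685 | 25 | 33 | 9.4% |
| All registered | 50 | 58 | 16.5% |

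If other registrations were also lost, for example by withdrawal, A is larger. At A = 8, every entrant could be one of the 32 joiners. At A = 33, at least one was an original child registered late. If joiners registered at 53% (32 × 351/667 ≈ 17), about 16 were.

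**3. Bias in the change-from-baseline contrast, central case.** Assumptions: 318 children with baseline and follow-up, 159 per arm; 33 follow-up-only entrants who differ from the others by d = 20 to 40 min/day; one baseline and one follow-up value per child; school effects and the midway round ignored. The baseline to follow-up correlation is r = 0.67 (Sample Size Calculation).

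With k entrants added to n children, the raw follow-up mean in an arm shifts by d × k/(n + k). In a mixed model with participant effects, the entrants also move the model-implied baseline mean by r times that amount. The shift in change is therefore (1 − r) × d × k/(n + k), or 0.33 of the raw shift.

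- 2:1 split (22 v 11): 22/181 − 11/170 = 0.0568. Raw shift: 1.1 to 2.3 min/day. Shift in change: 0.33 × these = 0.4 to 0.8 min/day.
- All in one arm (33 v 0): 33/192 = 0.172. Raw shift: 3.4 to 6.9 min/day. Shift in change: 1.1 to 2.3 min/day.
- Even split, similar entrants in both arms: 0.

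If the model constrains baseline means to be equal across arms, generalised least squares on the same inputs gives 0.7 to 1.3 min/day (2:1) and 2.0 to 3.9 min/day (all in one arm).

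The design target is 13.5 min/day.

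**4. Precision cost of restricting the set.** Inputs from Sample Size Calculation: SD 38, ICC 0.07, cluster-size CV 0.24, r = 0.67, α = .025, power 80%, 9 schools per arm. With m children per school, design effect = 1 + ((1 + CV²)m − 1) × ICC; SE = 38 × √(1 − r²) × √(2 × design effect/(9m)); detectable difference = 3.083 × SE by normal approximation.

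| Children | m | Design effect | SE | Detectable difference (min/day) |
|---|---|---|---|---|
| 351 | 19.5 | 2.374 | 4.640 | 14.3 |
| 318 | 17.7 | 2.238 | 4.733 | 14.6 |
| 293 (A = 58) | 16.3 | 2.135 | 4.816 | 14.8 |

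With a t distribution on 16 df, the first two rows become about 15.6 and 15.9.

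**The case against.** The case against has real force.

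- **What Table 3 shows.** It counts registration. It gives no SMS days, no registration dates and no split by arm. A reader might infer that selection differing by arm has occurred, or that late registrants knew their arm. The article supports neither: it describes release of allocation to the research team and does not say what control parents or newly arrived families were told. All 8 of the certain entrants could be joiners.
- **Mechanism.** The parent exercise is meant to draw parents to the family meetings, not to the questionnaire. Greater project awareness leading to registration is an inference.
- **Size.** A reader might take the raw follow-up shift of 3 to 7 min/day as the bias and conclude that late entry could produce an apparent effect by itself. The planned end point is change, where the figure is about a third of that. The assumed 20-40 min/day is itself about 0.5 to just over 1 SD.
- **Participation check.** A reader might suppose that the participant/non-participant comparison pools the arms. The article does not say whether it is pooled or split.
- **Scope.** The rule stands under Missing Data and concerns data sufficiency. A condensed article may leave the analysis set to a fuller document, and including children present at follow-up is a recognised open-cohort choice when schools are randomised.

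The first four points stand and limit the finding. The last stands only in part. The article does state a rule for who is analysed; as written it admits post-release entrants to a change-from-baseline comparison, and the intention-to-treat statement does not exclude them.

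**Conclusion.** The concern holds as a cheap improvement of moderate severity. The stated rule admits children first registered after their school's allocation was released, and Table 3 implies at least 8 new registrations, about 33 in the central case, and at most 58 if no other registrations were lost. That these fall after release rests on the order of baseline and release, since no registration dates are given.

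Entry that differs by arm is a plausible risk and has not been shown. Under the stated assumptions for 33 entrants, the bias is zero to about 2 min/day, or to about 4 if baseline means are constrained equal and every entrant is in one arm. Against 13.5 min/day this is unlikely to decide the trial's conclusion. It is still avoidable, and the set can be fixed now without knowledge of results: the article reports that no analysis of effects had been done as of March 2026.

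**What to change.** Before analysis starts:

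1. Define the primary analysis set as children enrolled at a participating school at baseline whose parent registered before that school's allocation was released. Analyse each in the school as randomised, including leavers and movers where SMS data exist.
2. Keep the all-available set, with late registrants and joiners, as a sensitivity analysis.
3. Report parent registration and SMS response by arm and by registration timing (before or after release).
4. Show the comparison of children with and without a participating parent by arm.

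The cost is one definition, which needs parents' registration dates and each school's release date. About 8 to 58 follow-up-only children, 33 in the central case, leave the primary analysis but stay in the sensitivity analysis. In the central case the detectable difference rises by about 0.3 min/day.
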